### Adverse events

All adverse events (AE) are recorded. Events related to the initial diagnosis for liver transplantation, to the transplantation procedure itself, or problems associated with routine procedures after transplantation, i.e. liver biopsy, are not to be noted as AE or serious adverse event (SAE) unless the investigator deems the events to be a cause of the study drug. All SAE potentially associated with the application of study medication must be documented on a "Serious Adverse Event" form which has to sent to the principal investigator (LKP, according to German Drug Law) within 24 hrs or latest on the following working day. The LKP ensures that SAE are reported to the safety board, ethics committees, and to further investigators, if applicable.

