### Objectives and endpoints

The primary objective of this trial is to demonstrate both efficacy and safety of glycine treatment compared to placebo in the postoperative period during the first eight days after liver transplantation and during the long-term follow-up. Secondary objectives are reperfusion injury to the graft and mortality. Furthermore, it will be investigated whether CyA-induced nephrotoxicity can be reduced by glycine.

Both AST and ALT peaks are expected to be surrogates of the extent of reperfusion injury. AST and ALT are the most common parameters for progression of liver related disease. An increase of these transaminases correlates with both primary failure of the organ and graft injury with subsequent organ dysfunction. Thus peak serum level of AST, measured at intensive care unit (ICU) entry and within the first 8 days after transplantation, has been chosen as the most important primary endpoint of this trial. Further primary endpoints ordered hierarchically are ALT peak during the same period and graft survival based on patients' death or announcement for re-transplantation (minimum observation period 31 days). The last reflects the potential clinical benefit for the patient.

Secondary endpoints are the effect of glycine on liver injury based on liver biopsy immediately after re-arterialisation (according to pathological report), total blood flow in portal vein and common hepatic artery 1 hour after reperfusion, graft injury based on both AST and ALT serum levels (area under the curve (AUC)), incidence of early graft failure based on peak of transaminases or clotting factor support, early onset of graft dysfunction based on Quick's value, serum bilirubin (AUC), and CyA-induced nephrotoxicity based on retention parameters during the first eight days after transplantation (AUC).

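### Complications put down to the disease, the operation or routine procedures enter the adverse event record only if blamed on the study drug, so their rates cannot be validly compared between arms

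*Protocol article*

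**What the plan says.** In the protocol article, the Adverse events section makes three statements in succession:

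- The general rule: "All adverse events (AE) are recorded".
- The exception. The classes are "Events related to the initial diagnosis for liver transplantation, to the transplantation procedure itself, or problems associated with routine procedures after transplantation", with liver biopsy named for the last of these. The instruction for such events reads "not to be noted as AE or serious adverse event (SAE) unless the investigator deems the events to be a cause", and the sentence ends by naming the study drug.
- The form: "All SAE potentially associated with the application of study medication must be documented" on the SAE form and sent on within a short deadline.

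Objectives and endpoints states: "The primary objective of this trial is to demonstrate both efficacy and safety of glycine treatment compared to placebo". Quality assurance says that an independent safety board watches the conduct of the trial and the SAE reports. Statistics and data management limits the interim analysis to safety parameters and the two transaminase peaks, and says that graft survival data are gathered only when the trial ends.

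**The concern.** The general rule and the exception cannot both be followed. The exception makes the recording of an event depend on a causal judgement in a single patient. That judgement is made blind. The first dose is given during the operation and the others on the seven mornings after it, when clinical bleeding or vascular and biliary complications can readily be put down to the surgery. Infection may be treated in the same way.

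An investigator looking at one patient has little basis for separating a drug effect from a transplant complication. A comparison of rates between randomised arms can separate them, but only if events are recorded without regard to presumed cause.

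At stake is the safety half of the primary objective. An excess of such complications on glycine could be largely absent from the AE and SAE tables, and the board would not receive those events as SAE reports. No later analysis plan can restore events that were never noted.

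**Working it through.** **1. Which harm data depend on attribution**

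The article gives no planned AE rate or AE power, so there is no figure of its own to reproduce. The sections compare as follows.

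| Harm information | Depends on attribution to the drug? | Where in the article |
|---|---|---|
| AE/SAE linked to disease, operation or routine procedures | Yes | Adverse events |
| SAE form, and so the SAE reports the board monitors | Yes | Adverse events; Quality assurance |
| AEs outside those classes | No | Adverse events |
| Death, listing for re-transplantation | No; graft survival compared at the end | Objectives and endpoints; Statistics and data management |
| ECG, vital signs, chemistry, haematology, coagulation, renal measures | No; scheduled to POD 8 | Table 2 |
| Coagulation factors, AT III, red cells, plasma given | No; to the morning of POD 8 | Randomization and treatment |

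The only item in the follow-up column of Table 2 is late graft failure. The table therefore schedules nothing after POD 8 that would pick up, for example, a biliary complication.

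**2. Size of the loss for the filtered classes (illustration)**

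Inputs: n = 65 per arm, from Sample size calculation. The true event rates p0 and p1 and the share f of events that pass the filter are assumptions; none comes from the documents. The share f is taken as equal in both arms because attribution is blinded. The test is two-sided at 0.05.

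The recorded rates are a = f·p0 and b = f·p1, with mean m = (a + b)/2. Then

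z = [(b − a) − 1.96·√(2m(1 − m)/65)] / √([a(1 − a) + b(1 − b)]/65), and power = Φ(z).

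For true rates of 40% v 60%:

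- f = 1: 0.40 v 0.60; z = (0.20 − 1.96 × 0.0877)/0.0859 = 0.33; power 0.63.
- f = 0.5: 0.20 v 0.30; z = (0.10 − 1.96 × 0.0760)/0.0754 = −0.65; power 0.26.
- f = 0.25: 0.10 v 0.15; z = (0.05 − 1.96 × 0.0580)/0.0578 = −1.10; power 0.14.
- f = 0.1: 0.04 v 0.06; z = (0.02 − 1.96 × 0.0382)/0.0382 = −1.44; power 0.08.

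Other assumed base rates with the same 20-point excess show the same pattern:

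| True rates | f = 1 | f = 0.5 | f = 0.25 | f = 0.1 |
|---|---|---|---|---|
| 20% v 40% | 0.706 | 0.357 | 0.189 | 0.098 |
| 30% v 50% | 0.646 | 0.295 | 0.155 | 0.084 |
| 40% v 60% | 0.628 | 0.259 | 0.135 | 0.075 |

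**3. Direction of the effect**

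With a common f, the ratio of recorded rates is unchanged: 0.60f/0.40f = 1.5 for every f. The absolute difference shrinks from 20 points at f = 1 to 2 points at f = 0.1. Equal true rates stay equal. The filter thus weakens a signal in either direction; it does not by itself favour an arm.

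**The case against.** The strongest reply is that much harm information bypasses the AE forms.

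- Death and re-transplantation listing form the third primary endpoint in all patients. Patients who die or are re-transplanted in the clinical period also receive the worst ranks in the non-parametric analyses.
- Renal harm is measured by serum creatinine and 24-hour urine, and nephrotoxicity is a secondary endpoint.
- Bleeding leaves traces in haematology, coagulation and blood-product use.
- The data management text puts all clinical and laboratory findings in the CRF, and safety parameters are evaluated at the interim.
- The excluded classes are worded more narrowly than routine care in general. Infection under immunosuppression or cyclosporine nephrotoxicity need not fall in them.
- The event rates and recording shares above are invented, and even full recording gives only about 63% power for a 20-point excess.

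Most of this stands, and it limits the point. A reader might infer that the arms cannot be compared for harm at all, that deaths would be missing from the final report, or that nearly every serious event is excluded. The listed routes contradict the first two inferences, and the article gives no figures to support the third.

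The reply does not remove the gap. Apart from graft survival, these routes are measurements that stop at about POD 8, not counts of clinical complications. The safety parameters in Table 2 contain no clinical events. The general CRF sentence does not override a specific instruction not to note an event as AE or SAE. A death after POD 8 that nobody attributes to the drug has no route to the board stated in the article while the trial is running. Although the article condenses a longer protocol, the exception is an explicit rule and not an omitted detail.

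**Conclusion.** The point holds for a defined part of the safety data. AE and SAE rates for events assigned to disease, surgery or routine procedures cannot be validly compared between arms. The board's SAE stream is filtered in the same way. This conflicts with the section's own opening sentence and with a primary objective that includes safety against placebo.

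Under the assumed rates, a 20-point excess that would be seen with about 63% to 71% power under full recording is seen with about 8% to 19% if a tenth to a quarter of events pass the filter. These figures assume that all the events counted belong to the excluded classes and that the recorded share is the same in both arms. The true share is unknown.

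It would go too far to say that the filter makes glycine look safe by construction. Attribution is blinded, so the expected effect is under-recording and lost power, not necessarily bias toward one arm. The rule should be changed, but the trial keeps a usable comparison of graft survival, scheduled measurements and other AEs.

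**What to change.** - Record every serious event in both arms whatever its presumed cause, with the investigator's causality assessment as a separate field.
- Confine any exemption for expected transplant-related events to expedited reporting.
- Give the safety board tables by arm of all serious events, with deaths and re-transplantation listings included as they occur and not held back until the end.
- Reconcile the opening sentence with the exception, and correct the phrase that makes the event a cause of the drug, which reverses cause and effect.

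The cost is a protocol amendment and some extra CRF data entry. Patients already have scheduled assessments to POD 8, so the added work in that period is modest. About 69 of 130 patients had been included by June 2005; on that count an amendment would cover the remaining 130 − 69 = 61. It would not by itself supply unrecorded events for patients already treated.

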### Quality assurance

The study is performed according to the principles of the ICH-GCP guidelines [39] and the ethical principles according to the current revision of the Declaration of Helsinki [40] and local legal and regulatory requirements. The trial is monitored by the KKS Heidelberg according to Standard Operation Procedures (SOP) that are based on ICH-GCP guidelines.

An independent safety board monitors closely the proper conduct of the trial and all SAE reports to ensure the safety of the subjects during the course of the study.

### Statistics and data management

All findings including both the clinical and laboratory findings are documented in the subject's case report form (CRF). All data are entered in a database as recorded. To ensure highest data quality a double data entry is performed. All missing data or inconsistencies are reported back to the center(s) and clarified by the responsible investigator. If no further corrections of the database are to be made it will be declared closed and used for statistical analysis.

The primary endpoints of the trial are peak serum levels of both AST and ALT measured within the first 8 days after transplantation, and graft survival based on patients death or announcement for re-transplantation.

Therefore the statistical hypotheses to be tested are as follows:

H0: AST_glycine _= AST_placebo _vs. H1: AST_glycine _≠ AST_placebo_,     (1)

H0: ALT_glycine _= ALT_placebo _vs. H1: ALT_glycine _≠ ALT_placebo_,     (2)

H0: S_glycine _= S_placebo _vs. H1: S_glycine _≠ S_placebo_,    (3)

While AST_glycine _and AST_placebo _represent the distribution of AST peaks in the glycine and placebo group, respectively, ALT_glycine _and ALT_placebo _represent the distribution of ALT peaks in the two groups, and S_glycine _and S_placebo _represent the survival functions of the two groups regarding graft survival.

The statistical hypotheses formulated above will be tested, each at the level of significance α (see below), in the strict order (1), (2), (3), i.e. a statistical testing procedure with a priori ordered hypotheses is applied [41].

All analyses are done according to the principle of intention-to-treat. Additional analyses (per protocol population, sensitivity analyses) will be described in the statistical analysis plan in more detail before closure of the database.

In the interim analysis only safety parameters and the primary endpoints AST peak and ALT peak will be evaluated. Data for the third primary endpoint (graft survival) are collected only at the end of the trial. The interim analysis is performed according to the group sequential design of O'Brien and Fleming [42]. The overall level of significance is α = 0.05, i.e. the level of significance for the interim analysis is α 1 = 0.0035, the level of significance for the final analysis is α2 = 0.0488.

If a patient dies or a re-transplantation has to be performed during the clinical period, serum measurements are not available. As this is the worst possible outcome, patients will be allocated the worst ranks for the respective (non-parametric) analyses.

Sensitivity analyses regarding the methods for dealing with missing values will be performed. Further details regarding the handling of missing data will be laid down in the statistical analysis plan that will be completed before unblinding of the data.

## Discussion

This ongoing clinical trial particularly demonstrates how a scientific hypothesis has been developed from bench to bedside, with classical investigations along the value chain of translational research from early in vitro work to in vivo experiments and finally from single case observations to the highest level of evidence, a randomized, prospective, controlled, double-blinded clinical trial. If previous findings are confirmed by the data of this ongoing clinical trial, glycine would improve the overall outcome after liver transplantation.
